**Revised estimates for the number of infections (secondary outcome):**

In stratum 1 (recurrence, no risk factors): Assuming an infection rate of 65% and for 15% absolute reduction to 50% we require 227 complete cases in each group for 90% power (1135 with four groups and 80% follow up) and 170 for 80% power (850 in total)In stratum 2 (risk factors, no recurrence): To detect a change from 40% to 30% we estimate we need 476 compete cases in each group for 90% power (2380 with four group and 80% follow-up) and 356 for 80% power (1780 in total).In stratum 3 (risk factors plus recurrence): To detect a change from 60% to 45% for 90% power we need 231 complete cases in each group or 1155 for four groups and 80% follow-up.

## 2.7 Data collection and management

### 2.7.1 Data collection

Data will be collected online at baseline, and then monthly for 13 months (52 weeks) using the trial and intervention website. Each month participants will receive an automated email and 1 week reminder to complete brief questionnaires, with more detailed questions at 6 months and 13 months. Non-completers at 6 months and 13 months will also be sent a paper questionnaire after 2 weeks and at 6 months (primary outcome) will also be followed up by telephone for limited responses after 3–4 weeks. Willing participants will complete an optional daily paper-based symptom diary should they develop an RTI during the trial period.

All data will be managed in accordance with the General Data Protection Regulation (GDPR) 2018. Electronic data will be stored on secure servers at University of Southampton and password protected. Anonymised paper questionnaires and diaries will be stored in locked filing cabinets prior to data entry and destroyed at the end of the study. Personal data will be collected for the purposes of study participation and kept separately from the questionnaire data for 10 years after the study has completed. Anonymous study questionnaires will be deposited in a secure data archive and made available for secondary data analysis, subject to further ethical approvals.

### 2.7.2 Data analysis

A detailed statistical analysis plan will be developed prior to data analysis. IBM® SPSS® software platform, Stata and Excel software will be used to evaluate outcomes.

The primary analysis will be based on those who report at least one infection in a normal year (before COVID). We will also conduct a sensitivity analysis to include all participants who included under the broader inclusion criteria (‘at-risk’ due to COVID).

The primary time point for analysis will be at 6 months. The analysis of the primary outcome and other continuous outcomes will compare all groups. For the incidence of infection data the primary analysis will be between each intervention group and usual care, and if any of these demonstrate an intervention is effective then we propose secondary comparisons between groups. A secondary analysis will use repeated measures over the year.

The particular regression models used will depend on the data and the patterns of residuals but we anticipate logistic regression models for dichotomous outcomes, negative binomial models for count data, and generalised linear mixed models will be used for continuous variables (all controlling for baseline values; stratification variables and potential confounding variables). Intention to Treat (ITT) analysis with missing data imputed (via chained-equations multiple imputation model) will be the primary analysis, and complete cases as a sensitivity analysis. Secondary analyses will follow a similar modelling approach to the primary analyses. The repeated measures analysis over the one-year period will allow for the clustering of observations within participants over time. Estimates will be provided for key subgroups (e.g. those with recurrent infections (>3/year), age >65, the presence and number of serious comorbidities). Results will be reported in line with the CONSORT guidelines.

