#### Reducing illness through modification of the nasal environment

Antiviral nasal sprays are commonly available to purchase over-the-counter in the UK. As medical devices, they have the potential to change the nasal environment, by creating a physical barrier to viral penetration or reducing viral replication [9]. Trials of antiviral nasal sprays compared to saline suggest there may be benefit in reduction of days of symptoms when used early in the illness, but the trial evidence is rather limited [10, 11]. Saline may also have a role in reducing symptoms associated with RTIs by irrigating the nasal passages and reducing levels of virus in the nasopharynx [9]. A systematic review of saline nasal irrigation (nasal rinses and sprays) in acute upper RTIs found some benefit in symptom control, although trials were small with a high risk of bias [12]. Whilst saline nasal sprays may have some effect in managing RTIs, they make for a useful comparison for the antiviral nasal spray as they have an equivalent method of delivery.

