### 2.3 Interventions

#### 2.3.1 Active treatment arms

Participants in the three active treatment arms will have access to a digital intervention (website available via desktop and smart devices) which has been developed using evidence-, theory- and person-based approaches [27]. Each intervention aims to facilitate behaviour change through three key mechanisms: (1) promotion of positive outcome expectancies (beliefs that the behaviour will prevent RTIs); (2) improved self-efficacy for performing the behaviour (mainly through clear instructions on how to perform the behaviour and advice on overcoming behavioural barriers); and (3) reduction of behavioural concerns (e.g. safety). The interventions include persuasive information about how each individual intervention may help reduce the number, duration and severity of RTIs experienced, clear instructions about how to perform the target intervention behaviour, and information to address key concerns that participants may have about engaging in the behaviour. Intervention-specific behaviour change techniques are discussed below.

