#### 2.5.4 Blinding/masking

Full blinding of trial participants to their intervention group is not possible. However, to reduce possible contamination (as the nasal sprays are available to purchase over-the-counter in pharmacies and supermarkets) the nasal sprays will be masked to their content by removing the manufacturers labels, and adding generic trial labels. As the nasal sprays in the study are medical devices there should not be a need to unmask them during the study. The GP practices are aware of the contents and other medical professionals involved in the care of participants can contact the study team for the same information if required. Staff responsible for data entry and data analysis will be blind to the treatment group.

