**Provisional sample size calculation agreed with the funder following the start of the COVID pandemic:**

To detect a 1-day difference among individuals having an infection (hazard ratio 1.2) for alpha of 0.01 and 90% power, we estimated we would require 147 individuals per group, and allowing for at least 15% of individuals to contract an infection during a 6-month winter/spring period 980 individuals per group. With four groups and 80% follow-up, then 4900 individuals would be needed. We also aim to estimate outcomes in the three strata (stratum 1 –recurrence, no risk factors; stratum 2—risk factors, no recurrence; stratum 3—risk factors plus recurrence) so planned to recruit 14,700 participants in total. We accepted that this would provide less power for our key secondary outcome (incidence of infections). However, the aim for the latter outcome is to compare each intervention with control, so using the arguments of Cook and Farewell, since each analysis of intervention versus control is independent, this should not require a conservative Bonferroni correction [28], and we can use an alpha of 0.05. Using these assumptions, the above sample size would provide more than 80% power to estimate a 25% reduction in the incidence of infections from 20% to 15% in each stratum and more than 90% power if the incidence of infections is 15% using all strata combined. We will update the sample size calculations based on the observed rates of infections in each season when the SAP is drafted.

**Revised estimates for the primary outcome based on data of the incidence of infections from the first two seasons (2020/21; 2021/22):**

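### Gel versus saline on infection incidence is compared only after an open-label contrast with usual care succeeds; its estimate should be reported regardless

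*Protocol article*

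**What the plan says.** Section 2.7.2 (Data analysis) treats two kinds of outcome differently. For days of illness and similar measures there is no condition: "The analysis of the primary outcome and other continuous outcomes will compare all groups". For incidence, the primary analysis is each intervention against usual care, and only "if any of these demonstrate an intervention is effective then we propose secondary comparisons between groups".

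Incidence carries weight in this trial. Section 2.6 plans sample sizes for it in each stratum and says of the provisional design: "We accepted that this would provide less power for our key secondary outcome (incidence of infections". The same section sets the error rate for these contrasts, arguing that "this should not require a conservative Bonferroni correction [28], and we can use an alpha of 0.05".

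Three other places bear on gel versus saline. The background says of saline sprays that "they make for a useful comparison for the antiviral nasal spray as they have an equivalent method of delivery". Section 2.5.4 states that "Full blinding of trial participants to their intervention group is not possible", but also that "the nasal sprays will be masked to their content by removing the manufacturers labels, and adding generic trial labels". Section 2.3.1 lists among the aims of every active arm's website "promotion of positive outcome expectancies (beliefs that the behaviour will prevent RTIs".

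**The concern.** Of the six pairwise contrasts among the four arms, only gel versus saline has both masked content and the same mode of delivery. The contrasts with usual care are open: active participants are encouraged to expect fewer infections, usual-care participants receive a page of advice, and infections come mainly from participants' own questionnaires. On incidence, the plan makes the better protected contrast wait for a less protected one. It gives no reason for treating incidence differently from the primary outcome.

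There is a statistical side too. Gel versus usual care and gel versus saline share the gel arm, so their estimates are positively correlated. Looking at the second only when the first is significant selects trials in which the gel arm happened to do well, and the shown gel-saline difference is then too large on average. When the condition fails, the comparison has no planned place. At stake is the reading of a modest gel effect on incidence, which is where a masked comparison is most useful for separating benefit from open-label reporting.

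**Working it through.** **Inputs from section 2.6.** Stratum 2: 40% versus 30%, 476 complete cases per group (90% power) or 356 (80%). Stratum 1: 65% versus 50%, 227 or 170. Stratum 3: 60% versus 45%, 231 (90%). Alpha is 0.05; two-sided is assumed. The provisional total is 14,700, with four groups and 80% follow-up.

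**Reproducing the plan's sample sizes.** n = [1.96·√(2p̄(1−p̄)) + z_power·√(p₁(1−p₁)+p₂(1−p₂))]² / (p₁−p₂)². This gives 226.2 and 169.3 (stratum 1), 476.0 and 355.9 (stratum 2), and 230.8 (stratum 3). All agree with the stated figures, so two-sided 0.05 without continuity correction fits.

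**Sizes examined per arm.**
- Single stratum: 356 and 476.
- Revised 90%-power incidence requirements combined: 227 + 476 + 231 = 934.
- Provisional total: 14,700 × 0.80 / 4 = 2,940.

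**Assumptions.** The documents give no expected gel-saline difference, so a range is used. Usual care is set at 40% throughout, including the combined sizes, although the strata differ. The gate opens when any intervention shows benefit over usual care at two-sided 0.05. Tests are unadjusted, and no open-label reporting bias is built in.

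**Hand check of gate opening, gel 35%, other arms 40%.** SE = √(2 × 0.375 × 0.625 / n), and P(gel beats usual care) ≈ P(Z > 1.96 − 0.05/SE).
- n = 356: SE 0.0363, 0.05/SE = 1.38, probability 28%.
- n = 476: SE 0.0314, 1.59, 36%.
- n = 934: SE 0.0224, 2.23, 61%.
- n = 2,940: SE 0.0126, 3.96, 98%.

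The other two arms add little.

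**Hand check of inflation.** If the gel contrast alone opened the gate, the mean shown gel-saline difference would be 0.05 + ρ·SE·φ(k)/P(Z > k), with k = 1.96 − 0.05/SE and ρ ≈ 0.49. For n = 934, k = −0.27 and φ(k)/P(Z > k) = 0.633, so the result is 0.05 + 0.49 × 0.0224 × 0.633 = 0.057, or 5.7 points.

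**Simulation** (four binomial arms, pooled z tests, at least 200,000 trials per scenario). Each cell gives the share of trials with the gate open, then the mean shown gel-saline difference in points.

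| Scenario (true difference) | 356 | 476 | 934 | 2,940 |
|---|---|---|---|---|
| Gel 30%, others 40% (10) | 80%; 10.6 | 90%; 10.3 | 99.5%; 10.0 | 100%; 10.0 |
| Gel 35%, others 40% (5.0) | 29%; 6.8 | 36%; 6.5 | 61%; 5.7 | 98%; 5.0 |
| Both sprays 30% (0) | 91%; 0 | 97%; 0 | 99.9%; 0 | 100%; 0 |
| Digital only 30% (0) | 80%; 0 | 90%; 0 | 99.5%; 0 | 100%; 0 |

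A repeat run gave 6.9 rather than 6.8 at n = 356. Before rounding, inflation in the 35% row is about 37%, 29%, 13-14% and under 1%. Of the gel-saline results that would be significant in that row, 49%, 43%, 26% and 2% fall in trials where the gate is closed.

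**Opposite-side case, gel 36% and saline 44%.** About 72%, 68%, 55% and 12% of significant gel-saline results fall in closed-gate trials at the four sizes.

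**Type I error.** With all arms at 40%, the gate opens in about 6.4% of trials. Gel versus saline is significant in 15-16% of those, but open and significant together occur in about 1% of all trials. Ungated, the rate is about 5%.

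**The case against.** The strongest reply is that this is an ordinary hierarchical rule. The primary objective (section 1.2.1) sets each intervention against usual care and does not list gel versus saline; the remark on saline is background. The rule lowers unconditional error rather than raising it. Gel versus saline on the primary outcome is ungated, so head-to-head evidence is not lost. Nothing says that incidence by arm will be suppressed, and a detailed statistical analysis plan is promised. All of this stands, and it is why the point is an improvement and not an error.

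A reader might infer more than the documents support:
- **That the comparison is generally withheld and generally inflated.** It is not. The distortion needs a gel effect well below plan, and it shrinks as strata are combined.
- **That a gel-saline difference straddling usual care would never be seen.** Any arm can open the gate, gel included. In the 36% versus 44% case, about 28% to 32% of significant results are still shown at single-stratum size.
- **That a trigger from the digital arm makes matters worse.** With digital at 30% and gel at 35%, the gate opens in 82-91% of single-stratum trials and the shown difference is about 5.05 and 5.03 against 5.0. An independent trigger removes the bias.
- **That masking makes expectations equal.** Section 2.5.4 gives contamination as its reason for masking and does not claim that participants cannot tell a gel from saline. Gel versus saline is better protected than the other contrasts, not fully blind.

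What the reply does not answer is why an estimate, as opposed to a claim, should depend on the gate.

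**Conclusion.** The point holds in a limited form. Section 2.7.2 makes gel versus saline on incidence depend on a positive open-label contrast, while the same contrast on the primary outcome is unconditional. At half the planned effect (gel 35%, others 40%), the gate stays closed in 71% and 64% of trials at 356 and 476 per arm, and the shown difference is roughly 37% and 29% too large. At 934 per arm the gate is closed in 39% and inflation is 13-14%. At 2,940 per arm the gate is closed in 2% and the bias is negligible. At the full planned effect, inflation is 6% and 3% at the two stratum sizes and about nil when strata are combined. There is no directional bias when both sprays work equally or when only the digital arm opens the gate.

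These sizes rest on a 40% usual-care rate, a two-sided 0.05 gate opened by benefit only, and no reporting bias. Reporting bias in favour of the sprays would open the gate more often.

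**What to change.** State in section 2.7.2, or in the statistical analysis plan, that the gel-versus-saline incidence estimate with its 95% confidence interval will be reported, labelled as secondary, whatever the contrasts with usual care show. Keep the present condition only for formal claims that one intervention is superior to another.

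The cost is one sentence and one further contrast from a model that will be fitted anyway; no sample size or data collection changes. The small downside is one extra unconditional secondary comparison.

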**Methods and design:**

Immune Defence is an open, parallel group, randomised controlled trial. Up to 15000 adults from UK general practices, with a comorbidity or risk factor for infection and/or recurrent infections (3 or more infections per year) will be randomly allocated to i) a gel-based nasal spray designed to inhibit viral respiratory infections; ii) a saline nasal spray, iii) a digital intervention promoting physical activity and stress management, or iv) usual care with brief advice for managing infections, for 12 months. Participants will complete monthly questionnaires online. The primary outcome is the total number of days of illness due to RTIs over 6 months. Key secondary outcomes include: days with symptoms moderately bad or worse; days where work/normal activities were impaired; incidence of RTI; incidence of COVID-19; health service contacts; antibiotic usage; beliefs about antibiotics; intention to consult; number of days of illness in total due to respiratory tract infections over 12 months. Economic evaluation from an NHS perspective will compare the interventions, expressed as incremental cost effectiveness ratios. A nested mixed methods process evaluation will examine uptake and engagement with the interventions and trial procedures.

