Stratum 1 (recurrence, no risk factors): Currently, in this group about 71%, compared to our original assumption of 15%, had an infection. Basing our recalculation on the more conservative lower limit of the 95% confidence interval of this estimate, we might assume that at least 65% of this group get an infection. Based on the original number per group of 147 (i.e. changing no other assumptions), we’d need 226 per group, and for 4 groups and with 80% follow up 1130. For 80% power, based on the original assumptions, we would require 111 per group. If 65% get an infection, then we would need 111/0.65 = 171 per group. For 4 groups with 80% follow up we would require 855 participants.Stratum 2 (risk factors, no recurrence): In this group, the observed infection rate has been around 40% compared to our assumption of 15%. On this basis, based on the original sample size calculation of 147 per group, we would require 147/0.40 = 368 per group. With 4 groups and 80% follow up this gives a total of 1472 for 90% power. For 80% power, we would require 1388 participants.Stratum 3 (risk factors plus recurrence): The infection rate is currently around 62% and follow up is just under 80%. On the basis of the original calculation, assuming at least 60% having an infection, we would need 245 per group, time 4 groups with 80% follow up gives 1225.

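### The missing-data check named in 2.7.2, complete cases, does not relax the missing-at-random assumption, so its agreement with multiple imputation would not show robustness to outcome-dependent dropout

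*Protocol article*

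**What the plan says.** Section 2.7.2 sets the missing-data strategy for the clinical outcomes. The intention-to-treat analysis with "missing data imputed (via chained-equations multiple imputation model) will be the primary analysis", and the check on it is "complete cases as a sensitivity analysis". The one other sensitivity analysis named there concerns who is analysed, not who is missing: "We will also conduct a sensitivity analysis to include all participants who included under the broader inclusion criteria". The section also states: "A detailed statistical analysis plan will be developed prior to data analysis".

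Other parts of the article bear on how data may come to be missing:

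- **Amount.** Section 2.6 allows for 20% loss: "With four groups and 80% follow-up, then 4900 individuals would be needed". For stratum 3 it reports experience to date: "The infection rate is currently around 62% and follow up is just under 80" per cent.
- **Masking.** Section 2.5.4 says: "Full blinding of trial participants to their intervention group is not possible". Only the contents of the two sprays are masked.
- **Collection.** Under 2.7.1, participants report monthly, online, through the site that also carries the interventions. Those who do not complete the 6-month questionnaire are sent a paper version after 2 weeks and are telephoned after 3–4 weeks for a limited set of answers.
- **Withdrawal.** Under 2.11.3, a participant who wants to stop the intervention is asked to stay in follow-up. One who does not confirm this is withdrawn and not contacted again, although data already given are kept.

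**The concern.** A sensitivity analysis is useful when it changes the assumption in doubt. Standard chained-equations imputation assumes that, given the variables in the imputation model, non-responders have the same distribution of illness days as responders. A covariate-adjusted complete-case analysis of a missing outcome assumes the same thing given only the covariates in the analysis model. Neither lets non-responders differ in illness days in a way the observed data do not capture.

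The design offers plausible routes to such a difference, and to its varying by arm. Participants know whether they have a spray, the behavioural programme or usual care. The active arms receive content meant to build belief in the intervention, while usual care receives a page of advice. Disengaging from an intervention and ceasing to report can go together because one website serves both purposes. The withdrawal rule in 2.11.3 gives, as its examples, people giving up a spray or the behavioural advice, a route with little counterpart in usual care.

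If those who stopped responding in an active arm had more illness than the model predicts, both analyses would overstate benefit, and their agreement could be reported as robustness.

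**Working it through.** **1. The plan's own allowance for missing data.** Section 2.6 gives 147 per group with an infection and an infection rate of 15%: 147 / 0.15 = 980 per group. With four groups and 80% follow-up, 980 × 4 / 0.80 = 4900, and for three strata 4900 × 3 = 14,700. Both totals match the article, so the planned missing fraction is m = 0.20.

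**2. Target effect per participant.** The target is a 1-day difference among those infected, but the primary outcome is total illness days over 6 months in everyone. If the intervention does not change incidence, the target per participant is 1 day × infected share, using the shares adopted in 2.6:

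- Stratum 2: 1 × 0.40 = 0.40 day
- Stratum 3: 1 × 0.60 = 0.60 day
- Stratum 1: 1 × 0.65 = 0.65 day

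**3. Departure that equals the target.** If non-responders in one arm average d more days than their imputed values, that arm's true mean exceeds the imputed mean by m × d. Setting m × d equal to the target gives d = target / m.

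| Stratum | Target per participant | d at 20% missing | d at 15% missing | d at 25% missing |
|---|---|---|---|---|
| 2 | 0.40 | 2.0 | 2.67 | 1.6 |
| 3 | 0.60 | 3.0 | 4.0 | 2.4 |
| 1 | 0.65 | 3.25 | 4.33 | 2.6 |

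The 20% column uses the article's follow-up figure. The 15% and 25% columns are assumed, to show the range. The relation is linear, so half the departure shifts the contrast by half the target.

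**4. Would the named check reveal it?** A simulation with assumed settings illustrates the point:

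- Two arms of 20,000, 20 repetitions, no true effect.
- Half of participants infected; illness days in the infected skewed, with mean depending on one baseline covariate.
- Usual care: 20% missing at random. Active arm: 20% missing, with the chance of being missing rising with illness days.
- Imputation and complete-case models both use arm and the baseline covariate.

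| Analysis | Estimated difference (days) |
|---|---|
| Full data, nothing missing | −0.01 |
| Complete cases | −0.94 |
| Multiple imputation | −0.94 |

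The two planned types of analysis agree with each other and are both about 0.94 day from the truth. The missing fraction is the same in both arms, so comparing follow-up rates by arm would not reveal the problem either. The size of the bias reflects the chosen settings. The close agreement is expected whenever the imputation model adds nothing beyond the analysis covariates.

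**The case against.** The strongest reply is that this is SAP material. The article condenses a fuller protocol and defers detail to an SAP that is not shown, where a delta-adjusted analysis would commonly be specified. Imputation with complete cases alongside is a conventional pairing, and nothing in 2.7.2 rules out a further check. A reader might infer that outcome-dependent dropout, as the main threat to the primary result, will go untested in this trial. The documents do not support that: what the article names is not shown to be all that is planned, and no section reports dropout by arm or by outcome. What does stand is narrower. The article names a check, and that check does not address this risk.

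Four other points deserve weight:

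- **Follow-up outside the website.** The paper questionnaire and telephone call at 6 months reach people who have left the site and are aimed at the primary time point. They should reduce missing data, but the roughly 20% allowed for is the share still without follow-up.
- **Monthly reports.** If the imputation model uses earlier monthly reports, it can recover information that complete cases discard, and the two analyses may then differ informatively. That helps with dropout explained by illness already reported. It does not help with illness after reporting stops, or with people who stop early.
- **Size of the departure.** The tipping values require an average shift across all of one arm's non-responders, beyond what the model explains. If the intervention also lowers incidence, as the secondary sample-size targets suppose, the effect in total days is larger and so is the tipping value.
- **Direction.** Active-arm participants who stay well might also stop reporting, which would bias against benefit. This argues for varying the shift both ways, not for omitting the analysis.

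**Conclusion.** The concern holds in a limited form. The missing-data check that 2.7.2 names rests on an assumption no weaker than that of the primary imputation, so agreement between them would say nothing about outcome-dependent dropout. With 20% missing in the arm concerned and no effect on incidence, a one-arm departure of 2.0, 3.0 or 3.25 days among non-responders (strata 2, 3 and 1) equals the whole target effect. Across 15% to 25% missing, the values run from 1.6 to 4.33 days. These are illustrations of sensitivity, not estimates of a bias known to exist. This is a cheap improvement to the plan, not an error that invalidates it.

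**What to change.** In 2.7.2 or the SAP, and before results are seen, pre-specify a delta-adjusted analysis on the imputations already planned:

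- Add a shift in illness days to the imputed 6-month values, varying it by arm and in both directions.
- Justify the range of shifts in advance. The values in the table above can help to set its scale, but the documents supply no range.
- For each contrast with usual care, report the shift at which the conclusion changes and say whether it is plausible.
- Keep complete cases as a supplementary analysis, and do not describe its agreement with imputation as evidence against not-at-random dropout.

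If the SAP already contains such an analysis, confirming this is enough. The cost is a few lines of text and code and no new data. The downside is a little more analysis work and a result that may look less firm.

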### 1.3 Trial design

Immune Defence is an open, randomised, parallel group, 4-arm trial evaluating i) a gel-based nasal spray, ii) a saline nasal spray, iii) a physical activity and stress management intervention and iv) usual care plus brief advice, in reducing duration and severity of RTIs in UK primary care, over 6 and 12 months. We will assess the impact overall and in at-risk subgroups of patients defined by whether they have a) recurrent infections, no risk factors; b) risk factors, no recurrent infections; or c) risk factors plus recurrent infections.

A nested mixed methods process evaluation will triangulate qualitative interview data with quantitative attitudinal and behavioural process measures and quantitative intervention usage data.

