### 2.2 Eligibility criteria

Participants will be eligible for the trial if they are 18 years and above, with a serious comorbidity or a risk factor for infection and normally experience one or more RTIs per year: Immunosuppression due to a serious illness or medication (e.g. chemotherapy); heart disease; asthma or lung disease; diabetes; mild hepatic impairment; stroke or other severe neurological condition; obesity (BMI>30); aged >65; 3 or more RTIs in the last year.

Participants will be excluded if they have any of the following identified through practice records: a terminal illness or are receiving palliative care; have a diagnosis of dementia; live in residential care; have pituitary adenoma. Participants will also be excluded through participant self-report if they: are pregnant/breast-feeding; regularly use nasal sprays to prevent respiratory infections; are allergic to nasal sprays; live in the same household as another participant; have been previously involved in the development phase of the trial.

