#### 2.5.3 Randomisation

The randomisation process (1:1:1:1) for this trial will be fully automated. The Immune Defence website software will generate a randomisation sequence and computer algorithm to block randomise participants to the 4 trial groups. As randomisation is automated, the sequence will be concealed from the trial team. Patients will be stratified on the basis of whether they are in a higher risk group (over 65 and/or having comorbid condition) and whether or not they have recurrent RTIs (≥3 in the last year) to three strata: stratum 1 (recurrence, no risk factors); stratum 2 (risk factors, no recurrence); stratum 3 (risk factors plus recurrence).

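### The analysis section cuts the recurrent-infection subgroup at more than 3 per year, while eligibility and stratification use 3 or more, and its examples omit the three strata

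*Protocol article*

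**What the plan says.** All references are to the protocol article.

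- **Section 2.7.2 (Data analysis)** promises estimates for "key subgroups (e.g. those with recurrent infections (>3/year), age >65, the presence and number of serious comorbidities". The same section describes its regression models as "all controlling for baseline values; stratification variables and potential confounding variables", and says that a detailed statistical analysis plan (SAP) will follow.
- **Abstract (Methods and design)** describes the population as including people with "recurrent infections (3 or more infections per year".
- **Section 2.2 (Eligibility criteria)** lists "3 or more RTIs in the last year" among the qualifying conditions. The registration table (Table 1) uses the same threshold.
- **Section 2.5.3 (Randomisation)** stratifies by risk group and by "whether or not they have recurrent RTIs (≥3 in the last year) to three strata": recurrence without risk factors, risk factors without recurrence, and both.
- **Section 1.3 (Trial design)** states: "We will assess the impact overall and in at-risk subgroups of patients defined by whether they have a) recurrent infections, no risk factors", and goes on to list the other two strata.
- **Section 2.6 (Sample size)** states: "We also aim to estimate outcomes in the three strata". It then gives separate revised sizes for each stratum.

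**The concern.** A threshold of more than 3 and a threshold of 3 or more define different groups, and the people in dispute are those at the entry threshold. Stratum 1 shows this most clearly. Its members have no risk factors, so the recurrence criterion is their only route into the trial. Under the cut-off in 2.7.2, a stratum 1 participant with exactly 3 RTIs would be neither recurrent nor at risk, a combination for which the design has no stratum.

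The list of examples adds to the difficulty. The strata are the subgroups that led the planners to triple the provisional sample, yet the section that specifies the analyses mentions them only as adjustment variables. The subgroups it does name are one-way factors.

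A SAP author working from 2.7.2 could carry the wrong cut-off forward. Two published definitions of one subgroup also leave room to choose between them after the data have been seen.

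**Working it through.** **1. The threshold, place by place**

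| Place | Recurrence means | Exactly 3 RTIs counts as |
|---|---|---|
| Abstract | 3 or more per year | recurrent |
| Table 1 | 3 or more in the last year | recurrent |
| 2.2 Eligibility | 3 or more in the last year | recurrent |
| 2.5.3 Randomisation | ≥3 in the last year | recurrent |
| 2.7.2 Data analysis | >3 per year | not recurrent |

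Four places agree and 2.7.2 is the exception. For whole-number counts, >3 means 4 or more, so the definitions differ only for people reporting exactly 3.

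**2. The strata, place by place**

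Section 1.3 names the three strata as subgroups, 2.5.3 randomises within them, and 2.6 sizes them. Section 2.7.2 adjusts for the stratification variables but does not list the strata among its examples.

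**3. Do the stated sample sizes depend on the cut-off in 2.7.2?**

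The plan's own step for the primary outcome is 147 infected per group (taken as stated) ÷ infection rate × 4 groups ÷ 0.80 follow-up.

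- Provisional: 147/0.15 = 980; 980 × 4/0.80 = 4900; × 3 strata = 14,700. Agrees.
- Stratum 1: 147/0.65 ≈ 226; 226 × 4/0.80 = 1130. Agrees.
- Stratum 3: 147/0.60 = 245; 245 × 4/0.80 = 1225. Agrees.

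For incidence in the two recurrence strata, a standard two-proportion calculation (two-sided alpha 0.05, 90% power, no continuity correction) gives 227 per group for 65% to 50% and 231 for 60% to 45%. These become 1135 and 1155 in total, as stated.

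The strata are defined on ≥3, so aligning 2.7.2 with them changes none of these figures.

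**4. Why no power loss can be claimed**

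Let f be the share of recurrent participants with exactly 3 RTIs. The documents do not give it, so the values below are assumptions. With a multiple k of the planned 147 infected per group, at alpha 0.01 and 90% planned power:

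power = Φ(√k × (2.576 + 1.282) − 2.576)

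- *If >3 were applied inside a single stratum*, k = 1 − f.
- *If the subgroup is one-way, as 2.7.2 words it*, it pools strata 1 and 3. At their planned 90% sizes this is 2 × 147 = 294 infected per group before exclusions, so k = 2(1 − f). This assumes the same standardised effect in both strata.

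| Assumed f | Single stratum: k, power | Pooled strata 1 and 3: k, power |
|---|---|---|
| 20% | 0.8, 81% | 1.6, 99% |
| 40% | 0.6, 66% | 1.2, 95% |
| 60% | 0.4, 45% | 0.8, 81% |

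The answer runs from a serious loss to none, depending on an unknown share and on which subgroup is meant. At f = 50% the pooled subgroup still holds 147 infected per group, which is the planned 90%. The table shows only that the documents do not determine a figure.

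**The case against.** The strongest reply is that this is a slip in one illustrative phrase. The list in 2.7.2 is introduced as examples, so it withdraws nothing from section 1.3, which commits to the three strata, or from section 2.6, which repeats that aim. The models still control for the stratification variables. A detailed SAP is to follow, and a condensed article need not print the full subgroup list.

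Most of this stands, and it rules out several stronger readings that a reader might infer:

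- *That the subgroup estimates will not be for the groups the trial was sized for, or that one-way factors have replaced the strata.* Sections 1.3 and 2.6 say otherwise, and a list of examples does not override them.
- *That the recurrent subgroup would be underpowered by a stated amount.* The share with exactly 3 RTIs is unknown, and a one-way recurrent subgroup pools two strata.
- *That the comparison is contaminated or loses the protection of randomisation.* The RTI count precedes randomisation, so arms within the >3 group are still compared as randomised. The subgroup merely stops matching the stratified blocks.
- *That exactly 3 is the commonest count.* No distribution is given.

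The reply does not remove the contradiction. Introducing the list as examples makes it incomplete; it does not turn >3 into ≥3. Nor is this a detail left to the SAP: the article prints a cut-off for a named key subgroup, and that cut-off disagrees with its own eligibility and randomisation rules.

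**Conclusion.** The concern holds in a narrow form. The recurrence cut-off in 2.7.2 conflicts with the abstract, Table 1, and sections 2.2 and 2.5.3. Followed literally, it puts participants with exactly 3 RTIs outside the recurrent subgroup although they were randomised as recurrent. The examples in 2.7.2 also fail to name the strata to which 1.3 and 2.6 commit.

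The consequence is limited to the membership of one named subgroup and the clarity of the prespecified subgroup list. The primary overall comparison, the stratum definitions and every stated sample size are unaffected. Comparisons between arms within the subgroup remain valid under either cut-off. The effect on power cannot be quantified from the documents. The conclusion rests on reading >3 as written; if it is a slip for ≥3, the correction is the same.

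**What to change.** In section 2.7.2, and in the SAP:

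1. Replace >3/year with 3 or more in the last year, stating that this is the recurrence definition used for stratification.
2. Name the three randomisation strata of section 1.3 as the prespecified key subgroups.
3. Keep age and the presence and number of comorbidities as further subgroups.

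The cost is about one line of wording. Stratum is already assigned at randomisation, so no new data are needed and no sample size has to be recalculated. The change should be made and dated before the outcome data are analysed, so that the choice of cut-off cannot be questioned later.
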